**Figure 1 fig1:**
[figure not shown]
Schedule of enrolment, interventions, and assessments of balanceHOME randomized control trial study.

### Participants, interventions, and outcomes

2.2.

#### Setting and eligibility criteria

2.2.1.

The recruitment of participants, the eligibility criteria assessment, obtaining informed consent (Supplementary material 3), and the intervention of the ACG will be carried out in the facilities of the neurorehabilitation center participant in the study. On the other hand, the pre-intervention, post-intervention, and 8-week follow-up evaluations will be carried out at the University of Valencia, while the interventions of the EG will be carried out at each participant’s home.

The recruitment and eligibility criteria assessments will be carried out by two different physiotherapists, who will verify the following inclusion criteria: (i) idiopathic PD; (ii) Hoehn & Yahr stage I-IV; (iii) independent gait with or without technical assistance; and (iv) stable parkinsonian medication for at least a month before the study star. On the contrary, the exclusion criteria will be as follows: (i) comorbidities that affect balance or walking; (ii) other neurological pathologies besides PD; (iii) chronic diseases not medically controlled; and (iv) participation in another physiotherapy program or sport activity during the intervention period or in the month before starting the study. Patient enrolment was started in August 2021 and is expected to be completed in August 2023. All patients are expected to have completed baseline testing in September 2023.

#### Interventions

2.2.2.

In total, two physiotherapy programs have been designed (balanceHOME and standard physiotherapy), both conducted two non-consecutive days per week, for 60 min each session over an 8-week period (Wong-Yu and Mak, 2015a,b; Atterbury and Welman, 2017; Santos et al., 2017; Soke et al., 2019), and each program will be conducted by different professionals. The sessions of both programs also have the same structure: warm-up (10′), central phase (45′), and cool-down (5′). The balanceHOME program will be performed for the EG, while the ACG will perform the standard physiotherapy program with the conventional goals and exercises for PD. This standard program will be developed in groups of six participants and conducted by a physical therapist and a rehabilitation assistant. The objectives included in the conventional program are (San Martín Valenzuela et al., 2020b): (i) cardiovascular training; (ii) upper and lower body strengthening; (iii) trunk strengthening and control; (iv) somatosensory balance; (v) dynamic balance; (vi) weight transfer and reaching; (vii) walking; (viii) fine motor skills; and (ix) stretching and relaxation.

On the other hand, the balanceHOME program consists of challenging balance exercises incorporated into functional daily tasks developed in-home and conducted by a different physiotherapist from the standard intervention. Additionally, whenever possible, the presence of a family member or caregiver in each session will be requested. The primary strategy will consist of splitting functional tasks of daily life (see Table 1) into static and dynamic balance components to facilitate an individualized progression in a functional context. Each exercise in the sequence will be developed in 30–60″ and will be repeated until the patient performs the necessary support reactions to avoid falling or has no imbalances to complete the exercise before continuing to the next level of the sequence. The following adaptations will be used to facilitate the execution of exercises from Table 1: (i) wide base of support; (ii) stable surfaces and flat ground; (iii) use of footwear; and (iv) hand-holding points. Conversely, the following balance disturbing strategies will be used before jumping into the next level of a sequence: (i) reduced support base; (ii) sloping floor and unstable surface; (iii) destabilizing forces (da Capato et al., 2015; Plate et al., 2016) by external imbalances; (iv) LoS exploration; (v) barefoot; and (vi) dual-task (cognitive and motor). Foam rubber, balls, and steps, as well as elements or set-ups from the home of each participant, will be used in each session. Regarding the warm-up phase, exercises related to breathing (Pitts et al., 2009; Reyes et al., 2013; van de Wetering-van Dongen et al., 2020), shoulder and pelvic girdle dissociation, joint mobility, postural changes (Stożek et al., 2016), muscle strengthening (Meyer et al., 1965; Kanegusuku et al., 2021), upper and lower limb mobility, and gait (Tomlinson et al., 2013; Tambosco et al., 2014) will be included. Finally, the cool-down phase will be focused on muscle stretching of the upper and lower limbs, trunk, head, and neck.

**Table 1 tab1:** Functional tasks and balance components from the balanceHOME program.

Functional task	*Static balance component*	*Dynamic balance component*
1. Reaching objects in sitting position	Lateral reaching outside the body midline. Frontal reaching outside the body midline.	Reaches outside the body midline while moving to standing position.
2. Looking in different directions during standing position	Head movement to different directions. To visualize objects in lateral visual field. To visualize objects in anterior visual field.	Talking to another person and walking. Avoid objects in the field of vision while walking.
3. Dressing during standing position	Fasten shirt buttons while standing. Tie your shoes while squatting.	Simulate pulling up your pants during the change from sitting to standing.
4. Manipulation above 90° of shoulder flexion during standing position	Cleaning a wall mirror while standing Reach for high shelf items.	Running and pulling back a curtain doing lateral gait.
5. Manipulation below 90° of shoulder flexion during standing position	To clean a piece of furniture. Watering plants.	Look for an object inside a bag while walking.
6. Ball throws and receptions during standing position	To throw an object at another person while standing. To catch an object in the air while standing.	To throw an object at another person while walking. To catch an object in the air the change from sitting to standing.
7. From seated to standing	Hold the semi squat position without upper limb support.	Go from sitting to standing position from a low seat.
8. From standing to squat to pick up objects from the ground	Pick up an object from the ground by flexing the trunk.	To pick up an object from the floor, with the semi-kneeling position.
9. From sitting on the ground to standing	Quadruped position alternating support between lower and upper limbs and change to three-points of support.	Moving from sitting on the floor to a semi-kneeling position and standing.
10. Steps	One foot on a step. To reach an object above 90° of shoulder flexion while on the steps.	To go up and down the steps. About passing the steps.
11. Stairs	One leg support with the freedom leg in different positions and heights.	To go up and down the stairs in single and dual-task.
12. Gait	Standing on irregular support base. Standing on narrow support base.	Gait with the support base altered. Walking through circuits with obstacles.
13. Manipulation objects during gait	Standing carrying an object of different sizes and different distances from the body.	Gait carrying an object of different sizes and different distances from the body.
14. Walking outside	Standing on the street with external cognitive and motor disturbances.	Gait on the street with external cognitive and motor disturbances.
15. Manipulation objects during walking outside	Standing outside and carrying an object of different sizes and different distances from the body.	Walking outside and carrying an object of different sizes and different distances from the body.
16. Coordination	To learn a sequence of movements with the arms while standing.	To learn a sequence of movements with the arms and legs.

#### Outcomes and participant timeline

2.2.3.

First, during the enrolment assessment, a standardized neurological clinical interview for Parkinson’s Disease (Supplementary material 4) will be performed. This interview includes questions related to habits, disease start, education, and working life. At the same time, weight, height, and body mass index will be measured with a wall stadiometer and a TANITA SC-240MA scale. The length of the lower limbs will also be measured during standing position with a tape measure from the anterior superior iliac spine and the medial malleolus. Asymmetries between the lower extremities greater than 1 cm will be considered within the first exclusion criteria (comorbidities that affect balance or gait). As mentioned above, each phase of the study has three evaluation moments: baseline (T0), post-8-week-training (T1), and follow-up (T2) at 8 weeks after the physiotherapy programs have finished. Assessments will be performed by a different physiotherapist from recruitment and treatment besides a neuropsychologist, both blinded to the treatment assignment. The participants will be evaluated in an ON-medication state (1 h after the dopaminergic dose) on the schedule described in Figure 1. In each measurement session, the severity of the disease (Hoehn and Yahr, 1967; Fahn et al., 1987), cognitive and mental status (Hamilton, 1959, 1960; Mahieux et al., 1995; Dubois et al., 2000; Marinus et al., 2003), perception on quality of life (Peto et al., 1995; Powell and Myers, 1995; Sandín et al., 2020), and balance and gait performance will be registered through clinical tests (Tinetti, 1986; Giladi et al., 2000; Kegelmeyer et al., 2007; Franchignoni et al., 2010) as well biomechanics instruments. Table 2 shows the scales and clinical tests that will be used to evaluate the participants. For balance biomechanics, assessment will be used a dynamometric platform (Dinascan/IBV Biomechanics Institute of Valencia, Valencia, Spain) and the NedSVE®/IBV software (version 5.3.0.1, Biomechanics Institute of Valencia, Valencia, Spain). Balance will be assessed through the Romberg tests under four static conditions with increasing difficulty (see Figures 2A,B): (i) eyes open; (ii) eyes closed; (iii) eyes open on a foam rubber; and (iv) eyes closed eyes on the foam rubber (thickness of 9 cm, 56.7 kg/m3 of density, and resistance of 25%) (Escamilla-Martínez et al., 2021). Participants were asked to find the most stable position while barefoot with their arms relaxed on either side of the body, with their heels together and toes apart at a 30° angle. Additionally, four static functional balance tests will be assessed, using the Romberg test protocol with their eyes open: (i) to see the time on an analogy clock (visual); (ii) to answer a simple question (verbal); (iii) to pour the contents of one glass into another (lower motor); and (iv) to simulate comb the hair (upper motor). The instructions for each task were standardized to ensure uniform execution of the gesture. Participants will be asked to remain as still as possible with their heads in a neutral position and their gaze forward, except for the lower motor test where they will be allowed to observe their hands. Each test will last for 30 s and will be recorded two times. Finally, dynamic balance will be assessed with stability limits and rhythmic weight shift tests on the platform (Balaguer García et al., 2012). In the stability limits test, participants from the Romberg position will have to move a cursor (which reflected the position of their CoP) toward eight targets (front, front-right, right, rear-right, rear, rear-left, left, and front left) visualized on a computer monitor placed in front at their eye level. Once the target is reached, the subject will have to maintain the posture with the CoP displaced at the limit of stability until the end of the 8 s of each test (Balaguer García et al., 2012). On the other hand, in the rhythmic weight shifts tests, subjects will have to move their CoP to the direction and velocity of a moving target visualized on the computer monitor (Balaguer García et al., 2012). Each dynamic test will be registered two times. As a result, the primary outcome of the study will be the CoP sway area, which is defined as the surface over which the CoP moves during the measurement and is a valid indicator of detecting postural control changes in dual-task conditions (Campolettano et al., 2020; Morenilla et al., 2020). The secondary outcomes are shown in Table 2 and consist of biomechanics and clinical variables related to static and dynamic balance.

**Table 2 tab2:** Summary of outcomes, measurement instruments, and assessment times.

Domain / Outcomes	Measurement instrument	Study period			
		Enroll (−t1)	Basal (t0)	Post (t1)	Follow (t2)
Enrollment					
Eligibility screen	Participation criteria	x			
Informed consent	Supplementary material 3	x			
Personal information	SNCI for PD (Supplementary material 4)				
Habits and working life					
Anthropometric data (weigh, height, body mass index, and lower limb length)	Wall stadiometer, TANITA SC-240MA scale, and tape measure	x			
Parkinson’s disease information					
Disease start and initial sign	SNCI for PD	x			
Parkinson’s disease severity	H&Y; UPDRS-III	–	x	x	x
Cognitive and mental status					
General cognitive state	MMP; SCOPA-COG	–	x	x	x
Executive cognitive function	FAB	–	x	x	x
Anxiety	HS for anxiety				
Depression	HS for depression	–	x	x	x
Balance and gait clinical performance					
Balance	MBT; TMT balance	–	x	x	x
Gait	TMT gait	–	x	x	x
Freezing of gait	FOG-Q	–	x	x	x
Quality of life					
Impact on life due COVID pandemic	CPI-Q		x	–	–
Perception of QoL due to Parkinson’s disease	PDQ-39		x	x	x
Confidence on self-balance	ABC scale				
Balance biomechanical performance					
*Static balance: Romberg and Functional test*					
ML and AP OP displacement (mm)	Dynamometric platform	–	x	x	x
Total CoP displacement (mm)		–	x	x	x
CoP displacement angle (°)		–	x	x	x
Mean CoP velocity (ms^−1^)		–	x	x	x
ML and AP CoP dispersion (mm)		–	x	x	x
CoP swept area (mm^2^)		–	x	x	x
*Dynamic balance: stability limits test*					
Reaction time (*s*)	Dynamometric platform	–	x	x	x
Maximum CoP displacement (%)		–	x	x	x
Success (%)		–	x	x	x
Directional control (%)		–	x	x	x
*Dynamic balance: rhythmic and directional control test*					
Directional adjustment (%)	Dynamometric platform	–	x	x	x
Perpendicular adjustment (%)		–	x	x	x
Gait biomechanical performance					
Speed (ms^−1^) and speed variability	3D photogrammetry Dynamometric platform	–	x	x	x
Stride length (m) and time (*s)*		–	x	x	x
Step length (m) and width (*m*)		–	x	x	x
Cadence (steps/min)		–	x	x	x
Double support time (%)		–	x	x	x
Stance and swing phase time (*s*)		–	x	x	x
Maximum ankle dorsiflexion during swing (°)		–	x	x	x
Maximum knee flexion during swing (°)		–	x	x	x
Maximum hip extension during stance (°)		–	x	x	x
Maximum hip flexion during swing (°)		–	x	x	x
Range of motion of lower limb joint (°)		–	x	x	x
CoP medial-lateral displacement (mm)		–	x	x	x
Mediolateral force amplitude (*N*)		–	x	x	x

SNCI for PD, Standardized neurological clinical interview for Parkinson’s Disease; H&Y, (Hoehn and Yahr, 1967); UPDR-III, Unified Parkinson’s Disease Rating Scale part III (Fahn et al., 1987); MMP, Mini-Mental Parkinson (Mahieux et al., 1995); SCOPA-COG, Scale for Outcomes in Parkinson’s disease-Cognition (Marinus et al., 2003); FAB, Frontal Assessment Battery (Dubois et al., 2000); HS, Hamilton scale (Hamilton, 1959, 1960); MBT, Mini BESTest (Franchignoni et al., 2010); TMT, Tinetti Mobility Test (Tinetti, 1986); FOG-Q, Freezing of gait questionnaire (Giladi et al., 2000); CPI-Q, Coronavirus psychological impact questionnaire (Sandín et al., 2020); PDQ-39, Parkinson’s Disease Questionnaire (Peto et al., 1995); ABC scale, Activities-specific Balance Confidence Scale (Powell and Myers, 1995). CoP, center of pressure.

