### Data collection, management, and statistical analysis

2.4.

Both evaluators (physiotherapist and neuropsychologist) will be responsible for exporting and filling in a database with variables from the scales and tests mentioned in Table 2 according to the code assigned to each patient to ensure his or her anonymity. To protect confidentiality during the study, the personal information of participants will be located separately from the main dataset on a local computer. The raw dataset will be maintained for 10 years after the completion of the trial with indefinite restricted access due to sensitive data. After the publication of the results trial, a fully anonymized patient-level dataset will be made publicly available on the registration trial website (clinicaltrials.gov). For participation in this study, no participant will receive any kind of incentives or compensation.

All analyses will be evaluated by intention-to-treat principles in terms of assignment to treatment and used a level of significance of 0.05. There are no interim analyses planned for this study. We will use the statistical software SPSS Statistics version 24.0 (IBM Corporation) for all the statistical analyses. Categorical variables were presented using frequency and percentage, and continuous variables as mean with standard deviation if they follow a normal distribution. To test for possible carryover effects of the experimental group, the sum of the values measured in the two periods for each subject will be calculated and compared across the two randomized groups (EG and PCG) using a test for independent samples (Serrao et al., 2019). There should be no difference if there is no sequence (balanceHOME program—usual daily activity or usual daily activity—balanceHOME program) effect.

To answer to the main aim of the study, a two-factor mixed multivariate analysis of variance (MANOVA) test was conducted to analyze the effects of within-subject factors (assessment times) and the between-subject factor (group) on the outcomes registered. The Bonferroni adjustment was used for *post-hoc* comparisons, and differences were declared statistically significant if the value of *p* was less than 0.05. Differences between groups for demographic outcomes were verified with a univariate analysis of variance (ANOVA) between-subjects test. Furthermore, to test for sex differences between groups, a chi-square analysis was used (San Martín Valenzuela et al., 2020b).

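### CoP sway area is named as primary but not tied to a condition, time or group contrast, and the stated main test neither isolates it nor controls error over its eight conditions

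*Protocol article*

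**What the plan says.** All references are to the protocol article.

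- **Primary variable (2.2.3):** "the primary outcome of the study will be the CoP sway area, which is defined as the surface over which the CoP moves". The reason given is that it "is a valid indicator of detecting postural control changes in dual-task conditions". The abstract names the same variable and adds no detail.
- **Conditions (2.2.3):** "Balance will be assessed through the Romberg tests under four static conditions with increasing difficulty" (eyes open or closed, with or without foam). In addition, "four static functional balance tests will be assessed, using the Romberg test protocol with their eyes open" (visual, verbal, lower motor, upper motor). "Each test will last for 30 s and will be recorded two times".
- **Times (2.2.3, Table 2):** baseline T0, post-training T1 and follow-up T2 in each phase. Table 2 gives the area one row for the Romberg and functional tests together, with T1 and T2 both marked.
- **Sizing (2.2.4):** a change in sway area and differences among three groups (EG, PCG, ACG), f = 0.15, two-tailed 5%, power 95%, giving 93 people, or 112 with dropout.
- **Allocation (2.3):** only EG and PCG are randomized.
- **Main analysis (2.4):** a two-factor mixed MANOVA, time by group, on the outcomes recorded, which are not listed. "The Bonferroni adjustment was used for" post-hoc comparisons, at 0.05.

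**The concern.** The article names a variable, but a primary endpoint also needs a condition (or a rule for combining conditions), a time and a contrast. With those open, several sway-area results could each be presented as the primary result once the data are in.

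The analysis section does not close the gap. The sample size is set for one variable at 5%, while the main test is multivariate. If gait, cognition or quality of life enter the same MANOVA, a significant omnibus result may reflect them and says nothing specific about sway area. The Bonferroni rule is not stated to cover the eight conditions. At stake is whether a reported positive primary result carries the 5% error rate on which the trial was sized.

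**Working it through.** **1. The plan's own figure.** For a repeated-measures group-by-time interaction, λ = f²·N·m/(1−ρ), df1 = (k−1)(m−1), df2 = (N−k)(m−1). The article gives f = 0.15 and three groups (k = 3). It does not give the number of measurements m or the correlation ρ. Assuming m = 6 and ρ = 0.5:

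- λ = 0.0225 × 93 × 6 / 0.5 = 25.11, df 10 and 450, power 0.952. This matches 93 at 95%.
- With m = 3 and ρ = 0.5, λ = 12.56, df 4 and 180, and 93 people give power 0.81.
- 93 × 1.2 = 111.6, rounded to 112.

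So 93 is consistent with a test on one variable in three groups. It does not correspond to a MANOVA on many outcomes.

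**2. Candidates for the primary result.** 4 Romberg + 4 functional = 8 conditions. With T1 and T2, 8 × 2 = 16 condition-by-time results. There are also three possible group pairs.

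**3. Does other text narrow the choice?**

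- *Condition.* The dual-task remark in 2.2.3 supports the choice of variable and does not define the endpoint. The Discussion expects improvement in single and dual conditions alike.
- *Contrast.* The Introduction's hypothesis sets home training against the traditional physiotherapy group. The only randomized contrast is EG versus PCG. The sample size refers to all three groups.
- *Time.* T1 and T2 are not ranked.

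**4. Error rate if each condition were tested at 0.05 and any one counted.** For independent tests the risk is 1 − 0.95^K: K = 8 gives 0.337 and K = 16 gives 0.560. For eight equally correlated two-sided normal tests at one visit (the correlation is an assumption, as the article gives none):

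| Between-condition correlation | Risk over 8 conditions |
|---|---|
| 0 | 33.7% |
| 0.3 | 30% |
| 0.5 | 25% |
| 0.7 | 19% |
| 0.8 | 16% |
| 0.9 | 12% |

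If T1 and T2 both counted without adjustment, with an assumed T1–T2 correlation of 0.5 to 0.7, the risk is 38–41% at between-condition correlation 0.5, 30–32% at 0.7 and 19–21% at 0.9. With all 16 independent it is 56%.

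**5. Effect of an omnibus gate.** If no sway-area result could be claimed unless the MANOVA were significant, the risk would be at most 5% when nothing in the model differs. If another outcome in the model truly differs strongly enough to open the gate almost always, the risk on sway area returns to the values in step 4.

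**6. After a fix.** One condition or composite, one time and one contrast gives 5%. Bonferroni over eight conditions uses 0.05/8 = 0.00625 and gives at most 5%.

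**The case against.** The article does single out one primary variable, separates secondary and tertiary tiers and sizes the trial on that variable. How two recordings are combined, and much model detail, may properly sit in a fuller protocol or SAP that is not shown. That is fair, and neither is counted here. It does not dispose of the point, because the article itself fixes the main test and the multiplicity rule, and as fixed these do not isolate the primary.

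Bonferroni for post-hoc comparisons would normally cover time and group pairs. This is a reasonable reading, so the two-visit figures hold only if that adjustment is not applied, and the group pairs are not added on top. The spread over conditions remains uncovered.

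A reader might infer that the plan carries a false-positive risk of 19–34% or more. The article does not support that. It nowhere says that conditions are tested separately at 0.05, that one success suffices or that no gate applies. Nor is 19% a floor, since correlations of 0.8 and 0.9 give 16% and 12%.

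A reader might also infer that the MANOVA cannot be computed. Table 2 lists 8 static measures; 8 × 8 conditions = 64 variables, and 64 × 2 time contrasts = 128 exceeds 93 − 3 = 90 error degrees of freedom. But the article does not say that all outcomes enter one model, and one MANOVA per test or domain fits the wording equally well. Even with all 64, an averaged-contrast test has 90 × 2 = 180 error degrees of freedom. A MANOVA confined to the eight sway-area variables would itself be a valid 5% test of them jointly, but the article does not specify one.

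**Conclusion.** The point stands in this form: the primary is not fixed to one condition or composite, one time and one contrast, and the stated main analysis neither isolates sway area nor is said to control error over its eight conditions. This follows from the text and needs no assumption.

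The size is conditional. About 12–34% at one visit assumes separate 0.05 tests, any one counting, no gate, and between-condition correlation from 0.9 down to 0. It is higher if both visits count unadjusted. A strict gate gives 5%, but only when no outcome in the model truly differs. Even the low end of the ungated range is more than twice the nominal 5%. This should be settled before outcome data are examined by group.

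**What to change.** Replace the MANOVA as the main test with one pre-specified univariate, baseline-adjusted analysis of sway area at T1, two-sided 5%, for one named contrast. For the conditions, choose one of two routes:

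- one composite, for example the mean over the four functional conditions, which fits the dual-task reason in 2.2.3; or
- all eight conditions as one family, controlled by Holm or Bonferroni.

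EG versus PCG is the only randomized contrast. The sponsor must reconcile that choice with the Introduction's hypothesis against the traditional physiotherapy group, and a functional-only composite with the Discussion's expectation for single and dual conditions. List single conditions (under the composite route), T2 and the other outcomes as secondary.

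**Cost.** Wording only, with no new data. Single-condition results become secondary or face a stricter threshold. The 95% power in 2.2.4 must be restated for the two-group test. As an illustration, two-thirds of 93 is 62, or 31 per arm. If f = 0.15 is read as a standardized difference of 0.30 (an assumption), the noncentrality is 0.30 × √(31/2) = 1.18 and power at T1 is about 21%. With baseline adjustment at an assumed correlation of 0.5 it is about 27%. Neither figure uses the crossover's second period.
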